| Disease activity | *DAS 28*  *ACR*  *RADAI*  *HAQ-score*  *VAS pain*  *VAS dis.act*  *Dis act Phys/observer*  *Dis act Pat*  *Morning stiffness*  *Short form health survey (SF 36)* |  |  | X | X | X | X | X | X |
| Bonemineraldensity | *DEXA-scan* |  |  | X |  |  |  |  | X |
| Serum for storage | *serologic markers, anti-antibodies, markers of boneformation & resorption* |  | X | X | X | X | X | X | X |
| Urine for storage | *markers for boneresorption & cartilage degradation* |  | X | X | X | X | X | X | X |
| Vital signs | *BP, pulse, temperature (oraal), weight, height* |  | X | X | X | X | X | X | X |
| Employement status | *jobstatus, sickleave, work resumation, % work* |  |  | X |  | X |  |  | X |
| Safety checks | *Infection , malignancy, hospital admittance, adverse events* |  |  | X | X | X | X | X | X |

Table of contents

[1. Introduction. 4](#__RefHeading___Toc60568766)

[Targeted therapy by TNF- blockade in RA. 4](#__RefHeading___Toc60568767)

[Objectives 6](#__RefHeading___Toc60568768)

[Research question(s) 6](#__RefHeading___Toc60568769)

[2. Investigational Plan 7](#__RefHeading___Toc60568770)

[Study medication and dosage 7](#__RefHeading___Toc60568771)

[Design. 7](#__RefHeading___Toc60568772)

[Duration of study 8](#__RefHeading___Toc60568773)

[Inclusion criteria: 8](#__RefHeading___Toc60568774)

[Exclusion criteria: 9](#__RefHeading___Toc60568775)

[Screenings procedures 10](#__RefHeading___Toc60568776)

[Variables and schedule of observations 10](#__RefHeading___Toc60568777)

[Background information 10](#__RefHeading___Toc60568778)

[Primary endpoint 11](#__RefHeading___Toc60568779)

[Secondary endpoints 11](#__RefHeading___Toc60568780)

[**Safety Variables** 12](#__RefHeading___Toc60568781)

[Adverse events 12](#__RefHeading___Toc60568782)

[**Laboratory variables** 12](#__RefHeading___Toc60568783)

[**Additional variables** 13](#__RefHeading___Toc60568784)

[**Clinical variables** 13](#__RefHeading___Toc60568785)

[Concomitant illnesses 14](#__RefHeading___Toc60568786)

[Concomitant treatment 14](#__RefHeading___Toc60568787)

[Concomitant medications 15](#__RefHeading___Toc60568788)

[Infections 16](#__RefHeading___Toc60568789)

[Pregnancy 16](#__RefHeading___Toc60568790)

[Overdosage 16](#__RefHeading___Toc60568791)

[Adverse events 17](#__RefHeading___Toc60568792)

[*Definition of serious and non-serious adverse events* 18](#__RefHeading___Toc60568793)

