## Design.

A monocenter prospective, exploratory study with a 1 to 2-week screening period and a 52-week follow-up period in 120 RA patients who receive adalimumab treatment in routine rheumatological practice and are TNF- blockade naïve or have failed to (or no longer) respond to other anti-TNF- treatment. There is no group of patients receiving control treatment, since it is considered unethical to withhold active treatment for 52 weeks in patients with active RA. Previous work has shown the efficacy of adalimumab in randomized trials (8;9).

The goal of the present study is to evaluate the response to adalimumab treatment in the TNF- blockade naïve patients and patients who failed on other prior TNF- blocking treatment. Therefore, responders will be compared with non-responders after all included patients have received anti-TNF- therapy in the form of adalimumab. Furthermore the goal is to understand more of the mechanisms underlying the response to anti-TNF- treatment. Adalimumab treatment will be discontinued in patients who do not fulfill the Eular response criteria for improvement (DAS 28) at week 16, according to routine clinical practice.

Patients who discontinue adalimumab at or after week 16 for lack of respons or other reasons will get a final clinical assessment as part of the close out visit. The reason for discontinuation will be noted in the case record form. These patients will not be followed for measurement of clinical parameters. In patients who respond, treatment will be continued and may be extended after the 52-week follow-up period of this study. Patients will be included starting January 2004.

Patients who drop out of the study before week 16 for any reason will be replaced by new patients, the reason of discontiuation will be noted in the case record form (*see withdrawl and replacement of patients)*

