## Duration of study

All patients participating in this study will receive 40 mg (0,8ml) adalimumab by subcutaneous injection every other week after fulfilling all inclusion criteria at baseline. All patients must have approval for reimbursement for TNF-blockade by their insurance company (DAS 28 >3.2). Patients will be seen during the study for efficacy and safety assessments at weeks 4, 16, 28, 40 and 52 using validated and generally accepted evaluation criteria (see laboratory and clinical variables). All visits will be fixed with reference to the baseline visit. Evaluation of ACR 20 and Eular response (DAS 28) will be performed at 16 weeks after initiation of adalimumab. The final clinical assessments will be performed at 52 weeks. If the patient does not meet the Eular criteria for moderate or good response at 16 weeks, adalimumab treatment is discontinued and no further assessments will be done.

Inclusion criteria:

1) Patients with the diagnosis rheumatoid arthritis according to the American Rheumatism Association (ARA) 1987 criteria and in ACR 1991 functional classes I, II, and III *(see appendix)*

2) The patient is naïve for anti-TNF- therapy or has failed other prior TNF- blockers

3) DAS 28  3.2

4) Age > 18 and  85 years old

5) Use concurrent methotrexate treatment (5 - 30 mg/week; stable since at least 28

days before initiation) during the study. Subjects may be taking nonsteroidal anti-

inflammatory drugs, provided the dose and frequency have been stable for at

least 28 days. Subjects may be receiving prednisone therapy  10 mg/day

provided that the dosage has been stable for at least 2 months prior to entry.

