### Secondary endpoints

The secundary endpoint of the study is the proportion of patients with a 20%, 50%, and 70% clinical improvement according to the ACR response criteria (11) at 4, 16, 28, 40 and 52 weeks after the initiation of adalimumab treatment. The parameters of disease activity e.g. tender joint count, swollen joint count, patient’s assessment of pain, patient’s global assessment, investigators global assessment, duration of morning stiffness, health assessment questionnaire, DAS 28, SF-36 (short form health survey) and RADAI (12) will be assessed at each time point starting from baseline. Also an assessment of the influence of adalimumab treatment on physical and mental wellbeing in relation to employment status, job-satisfaction and sickleave will be implemented in the form of questionnaires.

In addition we will look at the influence of adalimumab on bonemineraldensity, bonemetabolism.

This will be done by analysing serum and urine markers for bone formation and resorption, performing a DEXA scan before- and one year after adalimumab initiation.

We will look for genetic markers, e.g. genetic polymorphisms in TNF- genes, that may predict diagnosis, efficacy and side-effects of treatment in the individual patient.

In the future micro-array analysis may be done to screen for new markers that distinguish responders from non-responders. Also, immunological responses raised against adalimumab antibodies will be researched, comprising antibody formation and T cell responses.

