### Withdrawl and replacement of patients

Patients who drop out of the study before week 16 for any reason will be replaced by new patients, the reason of discontiuation will be noted in the case record form.

These patients will be seen for a final clinical assessment as part of the close out visit.

This visit will include physical examination, final assessment of disease activity (ACR, DAS 28, RADAI, SF 36), follow up of previous adverse events. Blood will be drawn for safety screening of clinical heamatology and chemistry parameters. Furthermore final immuno- serology to screen for auto-antibody formation (ANA, anti-ds DNA). Titers of IgM-RF and anti-CCP will also be drawn at this visit.

Premature discontinuation of study

The investigator has the right to discontinue this study at any time for medical and/or administrative reasons. As far as possible, this should occur after mutual consultation. Furthermore adalimumab treatment will be discontinued if there is no reimbursement by the insurance company.

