# 3. Methods of investigation

Clinical examinations

The clinical examinations including vital signs as well as safety assessments will be performed as usual in routine clinical practice. Blood will be drawn at the 7 visits 1 EDTA tube, 1 lithium heparine tube, 2 serum tubes and a 2.5 ml tube mRNA for storage at each time point. Serum will be immediately frozen at -70°C. The material will be used for detection of acute phase reactants, biologic markers (such as cytokines), anti-antibodies, leukocyte differential, and gene activation (micro array) in relation to the disease.

All samples must be clearly *labeled* (using labeling that can withstand freezing in liquid nitrogen/dry ice) including patient number and date and time of sampling.

Routine bloodtests for haematology and chemistry will be performed each visit including ESR and CRP as measures of disease activity. Routine urine samples are taken to check for proteinuria, blood and leucocyten and dipstick testing.

At baseline, after 28 and 52 weeks immunological assays e.g. anti-ds DNA (Crithidia), IgM rheumatoid factor, ANA and anti-CCP will be performed. This will be 1 serum tube at 3 visits.

Genetic polymorphisms

Only at baseline 1 additional EDTA tube will be drawn for DNA isolation and study of genetic markers, e.g. genetic polymorphisms in the TNF- alpha genes that may pedict efficacy and side-effects of treatment.

Bonemetabolism

Urine samples will be frozen from 6 visits for analysis of markers involved in bone resorption e.g. CTX I and CTX II for cartilage degradation.

Other markers for bone formation e.g. osteocalcin will be determined in the serum.

Bonemineraldensity

A DEXA scan will be performed at baseline and at 52 weeks to compare bonemineraldensity changes after adalimumab treatment.

Radiologic progression

X-rays of hands and feet will be performed at baseline and 52 weeks to evaluate disease progression using the modified Sharp v.d. Heijde scoring method.

Disease activity

This will be assessed by the DAS 28, the RADAI, HAQ questionnaires, the SF 36 (short health survey), response criteria number of clinical tests. Furthermore diverse analogue scales will be used to asses disease severity and pain in order to calculate the ACR response criteria.

Employment

At baseline, 28 weeks and 52 weeks questionnaires will be used to assess if adalimumab treatment has any influence on employment status, sickleave and workingcapacity (e.g.100 % fulltime or 50% parttime).

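### The close-out blood list has no stored serum, so patients who drop out before week 16 or stop between later visits have no anti-adalimumab antibody sample at failure

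*Protocol*

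**What the plan says.** **Scheduled sampling.** The Schedule of Observations (Protocol, row for stored serum) gives the purpose as "serologic markers, anti-antibodies, markers of boneformation & resorption" and marks weeks -2, 0, 4, 16, 28, 40 and 52. Section 3, Clinical examinations, agrees: "Blood will be drawn at the 7 visits 1 EDTA tube, 1 lithium heparine tube, 2 serum tubes", with uses that include "biologic markers (such as cytokines), anti-antibodies, leukocyte differential". After baseline, patients are seen "at weeks 4, 16, 28, 40 and 52" (Duration of study).

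**Stopping.** Patients without a moderate or good EULAR response at week 16 leave: "adalimumab treatment is discontinued and no further assessments will be done" (Duration of study). Under Design, those who discontinue at or after week 16 get a close-out visit, and then "These patients will not be followed for measurement of clinical parameters". That section does not list the blood tests. Patients who drop out before week 16 are replaced, but they too have a close-out visit (Withdrawl and replacement of patients).

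**Close-out blood.** The withdrawal section says "Blood will be drawn for safety screening of clinical heamatology and chemistry parameters" and adds ANA, anti-dsDNA, IgM-RF and anti-CCP. Laboratory variables confirms that this immunology panel is also done at close-out. Neither section names stored serum or antibodies to adalimumab.

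**Purpose.** Research question 1 puts antibody formation first among the factors that may separate responders from non-responders. Research question 8 asks about the T-cell origin of inhibitory antibodies to adalimumab. Secondary endpoints states that "immunological responses raised against adalimumab antibodies will be researched, comprising antibody formation and T cell responses".

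**The concern.** The Introduction proposes that antibodies to the drug may lead to loss or lack of response. To examine that in an individual patient, serum is needed near the time the drug fails. The protocol secures it only when failure falls on a scheduled visit.

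At close-out the patient is present, blood is taken, and disease activity is scored (ACR, DAS 28, RADAI, SF 36). The clinical outcome at failure is therefore recorded, but without the serum that could be related to it. A patient whose antibodies appear after the last scheduled sample would be classed as negative, or would have no on-treatment status at all. That misclassification falls on patients who stop, a group likely to include treatment failures.

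This is a matter of sample collection. An antibody window or a missing-data rule can be settled in an SAP, but a tube that was never drawn cannot be replaced.

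**Working it through.** The protocol gives no antibody rate, discontinuation rate, power or effect size, so it has no figure of its own to reproduce. The check is a count of samples, followed by one illustration that bears only on the caution.

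**Step 1: scheduled stored serum.** The schedule marks 7 visits, which agrees with the 7 in section 3. Two are at or before baseline (weeks -2 and 0), so 7 - 2 = 5 are after baseline.

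**Step 2: what each type of patient supplies if close-out adds none.** The spacing of post-baseline visits from week 4 is 16 - 4 = 28 - 16 = 40 - 28 = 52 - 40 = 12 weeks.

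| Patient stops | Post-baseline stored serum | Nominal gap from last sample to stopping |
|---|---|---|
| Before week 4 | none | no on-treatment sample |
| Between weeks 4 and 16 | week 4 | up to 12 weeks |
| At week 16 (non-responder) | weeks 4, 16 | none |
| Between weeks 16 and 28 | weeks 4, 16 | up to 12 weeks |
| Between weeks 28 and 40 | weeks 4, 16, 28 | up to 12 weeks |
| Between weeks 40 and 52 | weeks 4, 16, 28, 40 | up to 12 weeks |
| Completes week 52 | weeks 4, 16, 28, 40, 52 | none |

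With the permitted 7-day deviation at each visit, the longest gap is 12 + 1 + 1 = 14 weeks.

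**Step 3: tube burden of a remedy.** Each scheduled draw includes 2 serum tubes, so a completer gives 7 × 2 = 14. A patient who stops between weeks 40 and 52 has given 6 × 2 = 12, and one more at close-out makes 13. The storage-serum count stays below that of a completer, and the margin is wider for earlier stops.

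**Step 4: illustration for the caution.** Up to week 16 all patients still in the study have the same two post-baseline samples (weeks 4 and 16). To week 52 it is up to five for a responder against two for a week-16 non-responder. Suppose an analyst counted a patient as positive if ever positive to week 52, and that antibodies form at the same rate in both groups, with 10% positive by week 16 (assumed):

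- Constant rate: h = -ln(0.90)/16 = 0.00659 per week. By week 52, 1 - exp(-52 × 0.00659) = 0.29. Odds ratio, non-responder against responder: (0.10/0.90)/(0.29/0.71) = 0.27.
- Front-loaded formation, with 17% positive by week 52 (assumed): (0.10/0.90)/(0.17/0.83) = 0.54.
- A different model, with independent detection probability 5% per visit (assumed): 1 - 0.95^5 = 0.226 against 1 - 0.95^2 = 0.098, odds ratio 0.37. With 2% and 10% per visit it is 0.39 and 0.34.

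All of these arise with no true difference, but only under that definition.

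**The case against.** **The stronger inference.** From the count of five samples against two, a reader might conclude that the antibody-response comparison is biased against finding a link. The documents do not support that. Response is classified at week 16, when both groups have the same week-4 and week-16 serum, so an equal-window comparison is available. The protocol prescribes no ever-positive-to-week-52 definition. Its only named model, logistic regression, draws on baseline clinical features and patient characteristics. The choice of window is ordinary SAP content, and the SAP is not at hand.

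**The close-out list and week-16 non-responders.** The detailed list is written for patients who drop out before week 16. Non-responders at week 16 have stored serum from that visit, so the gap does not touch them. This stands and narrows the point. For those who stop after week 16, the protocol is silent on close-out bloods beyond the immunology panel; it does not say that serum is not stored.

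**Early drop-outs are replaced.** They may not count among the 120, which limits their weight in the primary percentage. It does not make their antibody status uninteresting, since the protocol still measures their disease activity at close-out.

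**Research question 1 may mean antibodies to earlier TNF blockers.** The Introduction says that those will be measured before adalimumab starts, so they are unaffected. But antibodies to adalimumab are named in research question 8 and under Secondary endpoints, and serum for anti-antibodies is stored throughout treatment.

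**The study is exploratory.** This is true. It limits the consequences, but it is no reason to leave out an inexpensive sample.

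**Conclusion.** The concern holds as a sampling gap. The close-out blood is itemised without stored serum, so patients who drop out before week 16 or stop between later visits have no listed anti-adalimumab sample at failure. The last on-treatment sample is either absent (before week 4) or up to 12 weeks old on the nominal schedule. This assumes that the close-out lists are meant to be complete and that the stop does not coincide with a scheduled visit.

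The number of patients affected and the effect on any estimate cannot be derived from the documents. Week-16 non-responders, 52-week completers and the measurement of antibodies to prior TNF blockers are not affected.

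Unequal sampling after week 16 is a caution and not an established bias. An ever-positive definition would pull the odds ratio toward 1 or below it; the illustrative 0.27 to 0.54 rests on assumed formation rates, on responders being sampled to week 52, and on a definition the protocol does not adopt.

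**What to change.** Add one storage-serum tube, for anti-adalimumab antibodies, to the close-out blood draw for every patient who discontinues, whether before or after week 16. State it in the withdrawal section, under Design for those who stop at or after week 16, and in the Schedule of Observations. If serum is already meant to be stored at close-out, saying so is enough. Where a patient stops at a scheduled visit, that visit's stored serum serves.

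The cost is one tube and one assay per discontinuing patient, at a draw that already takes place. No treatment or stopping rule changes.

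As a safeguard for the analysis, when antibody status is compared with week-16 response, take it from samples up to and including week 16 in all patients. This costs one sentence and may already stand in the SAP.

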# 3. Methods of investigation

Clinical examinations

The clinical examinations including vital signs as well as safety assessments will be performed as usual in routine clinical practice. Blood will be drawn at the 7 visits 1 EDTA tube, 1 lithium heparine tube, 2 serum tubes and a 2.5 ml tube mRNA for storage at each time point. Serum will be immediately frozen at -70°C. The material will be used for detection of acute phase reactants, biologic markers (such as cytokines), anti-antibodies, leukocyte differential, and gene activation (micro array) in relation to the disease.

All samples must be clearly *labeled* (using labeling that can withstand freezing in liquid nitrogen/dry ice) including patient number and date and time of sampling.

Routine bloodtests for haematology and chemistry will be performed each visit including ESR and CRP as measures of disease activity. Routine urine samples are taken to check for proteinuria, blood and leucocyten and dipstick testing.

At baseline, after 28 and 52 weeks immunological assays e.g. anti-ds DNA (Crithidia), IgM rheumatoid factor, ANA and anti-CCP will be performed. This will be 1 serum tube at 3 visits.

Genetic polymorphisms

Only at baseline 1 additional EDTA tube will be drawn for DNA isolation and study of genetic markers, e.g. genetic polymorphisms in the TNF- alpha genes that may pedict efficacy and side-effects of treatment.

Bonemetabolism

Urine samples will be frozen from 6 visits for analysis of markers involved in bone resorption e.g. CTX I and CTX II for cartilage degradation.

Other markers for bone formation e.g. osteocalcin will be determined in the serum.

Bonemineraldensity

A DEXA scan will be performed at baseline and at 52 weeks to compare bonemineraldensity changes after adalimumab treatment.

Radiologic progression

X-rays of hands and feet will be performed at baseline and 52 weeks to evaluate disease progression using the modified Sharp v.d. Heijde scoring method.

Disease activity

This will be assessed by the DAS 28, the RADAI, HAQ questionnaires, the SF 36 (short health survey), response criteria number of clinical tests. Furthermore diverse analogue scales will be used to asses disease severity and pain in order to calculate the ACR response criteria.

Employment

At baseline, 28 weeks and 52 weeks questionnaires will be used to assess if adalimumab treatment has any influence on employment status, sickleave and workingcapacity (e.g.100 % fulltime or 50% parttime).

Anti-adalimumab T cells

In order to analyse the presence of an anti-adalimumab specific T cell compartment and map the specific T helper epitopes in the adalimumab sequence, we will apply distinct computer algorithms to predict epitopes against which T cell reactivity may be induced. The predicted epitopes will be analyzed in the context of the patients HLA profile and on average 25 peptides will be analyzed per patient. We will measure T cell proliferation against the predicted epitopes *in vitro* using CFSE labeling and FACS analyses.

In a subset of patients (n=20 anti-adalimumab antibody formers, n=40 non anti-adalimumab antibody formers and n=40 adalimumab naïve patients) 45ml (5 tubes) of heparinized blood at one time point. will be collected to isolate PBMC’s by ficoll gradient centrifugation. The cells will be labeled with the fluorochrome CFSE and cultured for 7 and 14days in the presence of the predicted peptides. A separate informed consent will be asked for this subgroup of patients.

Data analysis

We will describe the proportion of patients responding to adalimumab treatment who are TNF-α blockade naïve and patients who lacked response to prior anti-TNF-α treatment in relation to laboratory parameters. We will report clinical parameters of arthritis activity as well as markers of bone and cartilage destruction. Logistic regression modeling will be performed to identify distinguishing or predictive factors of response to TNF- blockade among the clinical features at baseline and patient characteristics.

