Prospective study on the effects of adalimumab treatment in patients with rheumatoid arthritis who are naïve for TNF- blocking therapy and patients who do not respond (anymore) to prior treatment with other anti-TNF- medication.

Protocol version 2.1

04-02--2008

[name]

[name]

[name]

[name], PhD

Division of Clinical Immunology and Rheumatology, F4-218

Department of Medicine,

Academic Medical Center/University of Amsterdam

[name]

[contact] [contact] E-mail:[contact]

| *Schedule of Observations* |  | Screening | T=-2 | T=0 | T=4 | T=16 | T=28 | T=40 | T=52 |
| --- | --- | --- | --- | --- | --- | --- | --- | --- | --- |
| *Visit number* |  | **V0** | **V1** | **V2** | **V3** | V4 | **V5** | **V6** | **V7** |
| TNO/insurance request for approval | *(DAS 28)* | X |  |  |  | X |  |  |  |
| Demographics | *Age*  *Race*  *Height*  *Weight*  *Alcohol*  *Smoking* |  | X |  |  |  |  |  |  |
|
| DMARD & biological history | *DMARDs*  *Prednison*  *Biologicals* |  | X |  |  |  |  |  |  |
| Concommitant. medication |  | X | X | X | X | X | X | X | X |
| In- and exclusioncriteria |  | X | X |  |  |  |  |  |  |
| Informed consent |  |  | X |  |  |  |  |  |  |
| mRNA for storage |  |  |  | X | X | X | X | X | X |
| DNA sample (genetic polymorphisms) |  |  |  | X |  |  |  |  |  |
| X-thorax (< 3 mnd voor baseline) |  |  | X |  |  |  |  |  |  |
| PPD (<6 mnd voor baseline) |  |  | X |  |  |  |  |  |  |
| Virology screening | *Hepatitis B, C, HIV* |  | X |  |  |  |  |  |  |
| Urine -HCG | *pregnancy test* |  | X |  |  |  |  |  |  |
| IgM RF, anti- CCP, ANA, ds-DNA |  |  | X |  |  |  | X |  | X |
| Radiological progression | *Sharp modified by*  *Van der Heijde score* |  |  | X (<3mnd accepted) |  |  |  |  | X |
| (X-hands, feet) |
| Routine laboratory testing | *ESR, CRP, Hb, Ht, Leuco’s, Trombo’s, creatinin, ureum, Na, K, ALAT (SBPT), ASAT (SGOT), LDH, Gt, AF, glucose, bilirubine, alkaline phosphatase, protein and albumin,* |  | X | X | X | X | X | X | X |
| *Urine dipstick: glucose, protein, blood* |

| *Schedule of Observations* |  | Screening | T=-2 | T=0 | T=4 | T=16 | T=28 | T=40 | T=52 |
| --- | --- | --- | --- | --- | --- | --- | --- | --- | --- |
| *Visit number* |  | **V0** | **V1** | **V2** | **V3** | **V4** | **V5** | **V6** | **V7** |

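### The work questionnaire is at week 16 in the schedule but week 28 in the Methods text; if the text is followed, week-16 non-responders have no work data after baseline

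*Protocol*

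**What the plan says.** Two places in the protocol give times for the employment assessment.

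- **Schedule of Observations.** The time columns run "Screening | T=-2 | T=0 | T=4 | T=16 | T=28 | T=40 | T=52". The employment row, whose content is "jobstatus, sickleave, work resumation, % work", is marked at T=0, T=16 and T=52. The T=28 cell is empty.
- **Methods of investigation, Employment.** "At baseline, 28 weeks and 52 weeks questionnaires will be used to assess if adalimumab treatment has any influence on employment status". Week 16 is not mentioned.

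The Secondary endpoints section also lists work questionnaires but gives no times. Under Variables and schedule of observations, the protocol says that its variables are determined according to the schedule.

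Three other sections decide what follows for a patient without a response at week 16:

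- Duration of study: "at 16 weeks, adalimumab treatment is discontinued and no further assessments will be done".
- Design: patients who discontinue at or after week 16 have a final clinical assessment at a close-out visit, and then "These patients will not be followed for measurement of clinical parameters".
- Withdrawl and replacement of patients gives the only itemised close-out content: a physical examination, "final assessment of disease activity (ACR, DAS 28, RADAI, SF 36), follow up of previous adverse events", safety bloods and serology. It lists no work questionnaire.

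**The concern.** A mismatch of one visit in a secondary questionnaire would normally be an editorial matter. Here the two candidate visits fall on either side of the point at which non-responders leave the study. At week 16 every patient still in the study can complete the form, whatever the response. At week 28 only those who continued can.

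Research question 7 asks what adalimumab does to functioning at work and sick leave, and does not restrict the question to responders. If the form is first repeated at week 28, every post-baseline work observation comes from a group selected on week-16 response. Such a group could look better at work than all treated patients would. The study's central contrast, responders against non-responders, could not be made for change in work status at all. A form not collected at week 16 cannot be recovered at the analysis stage.

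**Working it through.** The protocol gives no figure to reproduce here. The check is a reading of the table, a trace of one type of patient, and one illustrative multiplication.

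**Step 1: is the table read correctly?** The row has a label cell, a detail cell and then eight time cells: Screening, −2, 0, 4, 16, 28, 40, 52. In the employment row the marks stand in the third, fifth and eighth time cells, that is T=0, T=16 and T=52. Two other rows of the same schedule test the alignment against the Methods text. The DEXA row falls at T=0 and T=52, as the text says. The autoantibody row has its follow-up marks at T=28 and T=52, again as the text says. So the employment mark at T=16 is not an artefact of how the table was extracted.

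**Step 2: follow a patient without a moderate or good EULAR response at week 16.**

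| Time | Under the schedule | Under the Methods text |
|---|---|---|
| Week 0 | work form | work form |
| Week 16 | work form | none |
| Week 28 | has left | has left (form was due) |
| Week 52 | has left (form was due) | has left (form was due) |
| Work forms after baseline | 1 | 0 |

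The middle assessment differs by 28 − 16 = 12 weeks. The close-out visit does not fill the gap, because no section provides for the work questionnaire there. The SF-36 is on the itemised close-out list, but the schedule lists it separately from the employment items, and it is not a record of job status or sick leave.

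**Step 3: how many patients?** The inputs are 120 planned patients (Design) and a week-16 non-response rate. The protocol gives no rate for adalimumab. Its introduction cites at least 30% non-response for infliximab, so 20–40% is taken as an assumed range.

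Patients with no post-baseline work data under the Methods text = 120 × non-response rate:

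- at 20%: 120 × 0.20 = 24
- at 30%: 120 × 0.30 = 36
- at 40%: 120 × 0.40 = 48

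Under the schedule, patients who reach week 16 are due one on-treatment work form. Drop-outs before week 16 are to be replaced, so that should be close to all 120.

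**Step 4: week 52.** Non-responders have left by then under either version. Choosing between the two passages adds or removes the middle value only, and does not change who is seen at week 52.

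**The case against.** The strongest reply is that the protocol already indicates which version governs. It says that variables are determined according to the schedule, and the schedule has week 16. On that reading no data are lost and the Methods sentence is a slip. This largely stands: the loss arises only if staff or the case record form follow the Methods sentence. It does not remove the need for a correction, because that sentence is explicit and is the one place in the text that gives times for this questionnaire.

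Several stronger readings are tempting, and the protocol does not support them:

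- **That different sites would collect at different weeks and the data could not be pooled.** The Design section describes a single-centre study. The remaining risk is inconsistent collection within that centre.
- **That the close-out visit for week-16 non-responders expressly omits the questionnaire.** The itemised list is written for drop-outs before week 16. For later discontinuations the Design section promises a final clinical assessment without itemising it. What can be said is that no section provides for the form at close-out.
- **That work outcomes would show improvement by selection.** The protocol has no work data from which to judge direction or size. They could look favourable; more than that cannot be said.
- **That using week 16 cures the selection.** As Step 4 shows, week 52 remains confined to continuing patients.

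It is also fair to say that this is one secondary outcome in an exploratory study, touching neither the week-16 response endpoint nor safety. Which work comparison is the main one can be left to an analysis plan.

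**Conclusion.** The contradiction is real and should be corrected: weeks 0, 16 and 52 in the schedule against weeks 0, 28 and 52 in the Methods text. Its consequence is conditional. If the Methods text is followed, week-16 non-responders contribute no work data after baseline, and post-baseline results for research question 7 describe only patients who continued past week 16. The illustrative size is 24–48 of 120 patients, resting wholly on the assumed 20–40% non-response. If the schedule is followed, this loss does not occur. A reader might infer that the plan as a whole leaves non-responders without work data; it does not, because the schedule covers them at week 16. The limit on week-52 data holds either way and needs to be stated when those results are reported.

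**What to change.** 1. In Methods of investigation, Employment, change the time points to baseline, week 16 and week 52, so that they match the schedule.
2. Add the work questionnaire to the content of the close-out visit, for patients who stop before, at or after week 16.
3. Report week-52 work results as applying to patients still on treatment.

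The cost is one corrected sentence and one extra form at visits that already exist. The week-28 assessment named in the text is given up, but the schedule never included it.
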